The Safety and Short-Term Efficacy of Aliskiren in the Treatment of Immunoglobulin A Nephropathy – A Randomized Cross-Over Study

Principal Investigator:

[name], Consultant & Honorary Professor

Co-Investigator:

[name], Professor

Department of Medicine & Therapeutics, The Chinese University of Hong Kong, Prince of Wales Hospital, Shatin, Hong Kong.

Protocol: AIgA / CRE-2009.057-T

Protocol date: 23 February 2009

ABSTRACT

Immunoglobulin A (IgA) nephropathy is the most common type of primary glomerulonephritis in the world. Current treatment with angiotensin converting enzyme (ACE) inhibitor and angiotensin receptor blocker (ARB) is not entirely effecive. Aliskiren, a direct renin inhibitor, acts on the rate limiting step of the renin-angiotensin axis. In addition to lowering the blood pressure, recent study in diabetic nephropathy suggests an independent anti-proteinuric effect. We plan to conduct a a randomized placebo-control cross-over study to evaluate the safety and efficacy of aliskiren in the treatment of IgA nephropathy. We plan to recruit 57 patients with biopsy-proven IgA nephropathy and persistent proteinuria despite conventional therapy. They will be randomized to aliskiren for 16 weeks or no treatment, followed by cross over to the other arm after a washout period. Proteinuria, albuminuria, renal function, serum and urinary markers will be quantified. This study will explore the potential anti-proteinuric effect of aliskiren in the treatment of IgA nephropathy, which has no specific treatment at present.

BACKGROUND

Immunoglobulin A (IgA) nephropathy is the most common type of primary glomerulonephritis worldwide [1]. It causes end stage renal disease in 15 to 20% of individuals within 10 years of onset [2], and in 30 to 35% of individuals within 20 years of onset. Proteinuria, an elevated serum creatinine concentration, hypertension, and advanced, chronic disease in kidney biopsy predict progression [2, 3].

The optimal therapy of IgA nephropathy remains unknown. Angiotensin-converting enzyme (ACE) inhibitors or angiotensin receptor blockers (ARB) reduce proteinuria in short-term trials [4-7] and retard the rate of progression of renal function deterioration in chronic, proteinuric nephropathy [7,8]. However, ACE inhibitor and ARB may not accomplish enough among high-risk patients because there exist bypass mechanisms and inhibition of the renin-angiotensin axis (RAS) is usually incomplete [9].

Renin inhibition is a new option to block the RAS at the first rate-limiting step. Preliminary data suggest a more complete suppression of the intra-renal RAAS with direct renin inhibition as compared with ARBs and ACE inhibitors [10]. Renin inhibition with aliskiren lowers blood pressure in hypertensive patients [11,12]. There is early evidence that direct renin inhibitors may also have anti-proteinuric effect. In nondiabetic hypertensive patients, renin inhibition with remikiren leads to albuminuria reduction [13].Recently, Persson et al [14] showed that aliskiren, the only direct renin inhibitor on the market, reduced 24-hour blood pressure, and this was associated with a reduction in albuminuria in type 2 diabetic patients. However, the efficacy of direct renin inhibitor for the treatment of non-diabetic chronic proteinuric kidney diseases has not been evaluated.

Although blockers of the RAS reduce blood pressure, their therapeutic benefit in proteinuric kidney diseases is generally believed to be the result of RAS inhibition. Along this line, human study of intra-renal ACE and type 2 ACE (ACE2) expression has long been hampered by the need of renal biopsy. In the last few years, with the development of reliable RNA extraction technique from urinary sediment and reverse transcription real-time quantitative polymerase chain reaction (RT-QPCR), measurement of mRNA expression in urinary sediment has become an emerging tool for the study of kidney diseases [15,16]. We recently showed that in the patients with diabetic nephropathy treated with ACE inhibitor, there was a significant inverse correlation between the degree of proteinuria and rate of renal function decline and urinary ACE2 expression [17], and urinary expression of synaptopodin was lower after 12 weeks of ACE inhibitor and ARB combination therapy [18], suggesting a reduction in urinary podocyte loss. Taken together, gene expression study of urinary sediment may provide insight to the status of intra-renal renin-angiotensin system.

OBJECTIVE

The primary objective of the present study is to evaluate the safety and short-term efficacy of aliskiren, a direct renin inhibitor, on proteinuria reduction in patients with IgA nephropathy. The secondary objective is to evaluate the effect of aliskiren treatment on the serum cytokine and urinary gene expression profile in patients with IgA nephropathy.

PATIENTS AND METHODS

This is an placebo-controlled cross-over study. We plan to recruit 57 patients with biopsy-proven IgA nephropathy.

# Inclusion criteria

- aged 18-65 years
- requires anti-hypertensive therapy
- renal biopsy confirmed the diagnosis of IgA nephropathy
- proteinuria > 1 g/day (or proteinuria > 1 g/g-Cr) in 3 consecutive samples within 12 weeks despite ACE inhibitor or ARB treatment for at least 3 months
- estimated glomerular filtration rate > 30 ml/min/1.73m2
- willingness to give written consent and comply with the study protocol

# Exclusion criteria

- Patients who are diabetic, and patients with systemic diseases that may cause IgA nephropathy or another nephroapthy.
- Pregnancy, lactating or childbearing potential without effective method of birth control
- Severe gastrointestinal disorders that interfere with their ability to receive or absorb oral medication
- History of malignancy, including leukemia and lymphoma within the past 2 years
- Systemic infection requiring therapy at study entry
- Any other severe coexisting disease such as, but not limited to, chronic liver disease, myocardial infarction, cerebrovascular accident, malignant hypertension
- History of drug or alcohol abuse within past 2 years
- Participation in any previous trial on aliskiren or other renin inhibitor
- Previous treatment with fish oil, steroid, cytotoxic agents, or aldosterone antagonist
- History of treatment with other drugs that may affect proteinuria within past 2 years
- Patients receiving treatment of corticosteroid
- On other investigational drugs within last 30 days
- History of a psychological illness or condition such as to interfere with the patient’s ability to understand the requirement of the study
- History of non-compliance
- Known history of sensitivity or allergy to aliskiren or other renin inhibitor

# Treatment regimen and dosage adjustment

After informed consent, each subject will be randomized to receive either oral aliskiren 300 mg/day or placebo for 16 weeks, followed by a washout period of 4 weeks, then crossed over to either placebo or aliskiren for another 16 weeks:

[figure not shown]

The appearance, packaging and labelling of the study medication and placebo would be identical. Individuals were randomised by a computer-generated list, which is used for packaging of the study item and then maintained by a third party that is not involved in the conduction of the study. Marked drug packs (35 capsules for each 4 week supply) will be designated for each patient. Both patients and investigators will be blinded. Results of biochemical tests will completed before the randomisation code is broken at the end of the study.

Based on the result of published study [Persson F, Rossing P, Schjoedt KJ, Juhl T, Tarnow L, Stehouwer CD, Schalkwijk C, Boomsma F, Frandsen E, Parving HH. Time course of the antiproteinuric and antihypertensive effects of direct renin inhibition in type 2 diabetes. Kidney Int 2008; 73: 1419-1425], a washout period of 4-weeks would be sufficient and baseline proteinuria level could be re-established.

During follow up visits, aliskiren will be dispensed by a dedicated research nurse; clinicians will be blinded from the treatment allocation.

*Concomitant therapy*

Prior to enrollment, all of the patients will be stable while receiving ACE inhibitor or ARB. Anti-hypertensive therapy will be titrated throughout the study period to maintain the blood pressure below 130 / 80 mmHg.

*Visit schedule*

Follow up visits will take place according to the following schedule:

- week –4 (screening)
- weeks 0, 2, 4, 8, 12, 16, 20, 22, 24, 28, 32, 36 and 40 (final visit)

During every visit, the following parameters will be measured: body weight, blood pressure, pulse, adverse effects of treatment, complete blood picture, differential white cell count, renal function test, liver enzymes, serum calcium, phosphate, and early morning urine collection for protein-to-creatinine and albumin-to-creatinine ratio. Renal function is determined by the estimated glomerular filtration rate (GFR) according to a standardized formula validated in Chinese [19]. Serum fasting glucose and lipid profile will be measured at 0 and 16 weeks. Proteinuria will be measured by a turbidimetric technique with the Modular Analytics (Roche Diagnostics, Switzerland). Urinary creatinine (Jaffe's kinetic method) and albumin (immunoturbidimetry method) were also measured on the Hitachi 911 analyzer (Boerhringer Mannheim, Mannheim, Germany), using reagent kits supplied by the manufacturer.

During week 0, 4, 16, 20, 24 and 36, whole stream early morning urine will be collected for the study of gene expression in urinary sediment. The method of specimen handling has been described in our previous studies [16-18]. Based on these studies, the target genes to be quantified include nephrin, podocin, synaptopodin, ACE, ACE2, transforming growth factor beta-1 (TGF-1), connective tissue growth factor (CTGF), and hepatocyte growth factor (HGF). Urine supernatant will also be saved for the assay of TGF-1, CTGF and HGF by standard ELISA. At the same time points, we will also serum level of C-reactive protein (CRP), TGF-1, and angiotensin II will be measured by ELISA, as well as plasma renin activity (PRA) by conventional methods.

*End points*

Primary end point of the study is the change in the degree of proteinuria and albuminuria. Average levels proteinuria and albuminuria levels at –4 and 0 week will be taken as the baseline. Secondary end points include the rate of decline of estimated GFR (as determined by the least square method), and change in serum and urinary inflammatory markers.

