## Statistical analysis

Data will be expressed in mean  SD. The change in proteinuria, renal function and other inflammatory markers before and after treatment will be compared by paired Student’s t test or Wilcoxon’s matched-pairs signed-rank test as appropriate. Calculation will be performed by SPSS for Windows software version 11.5 (SPSS Inc, Chicago, IL).

JUSTIFICATION

The sample size is estimated by the Power Analysis and Sample Size for Windows software (PASS 2000, NCSS, Kaysville, Utah). We expect baseline proteinuria to be around 2.0 ± 0.75 g:g-Cr [20]. Given that in the recently published AVOID study [21] aliskiren led to a 20% additional proteinuria reduction on top of losartan 100 mg, a sample size of 57 would be needed to achieve 80% power, with a significance level (alpha) of 0.05, using a two-sided paired t-test.

TIMETABLE OF WORK

It takes 24 months to complete the study:

Enrollment of case September 2009 to November 2010

Follow up of case December 2010 to August 2011

Analysis and write up report September 2011 to December 2011

REFERENCE

1. D’Amico G. The commonest glomerulonephritis in the world: IgA nephropathy. Q J Med 1987; 245: 709-727.
3. Haas M. Histologic subclassification of IgA nephropathy: a clinico-pathologic study of 244 cases. Am J Kidney Dis 1997; 829-842.

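### The paired t or signed-rank test named for this two-sequence cross-over leaves out period and sequence; analysing by randomised sequence is an almost free improvement

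*Protocol*

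**What the plan says.** Protocol, Treatment regimen and dosage adjustment: each patient begins with a 16-week course of aliskiren or placebo. What comes next is given as "followed by a washout period of 4 weeks, then crossed over to either placebo or aliskiren for another 16 weeks". The design therefore has two periods and two sequences. On allocation the section says "Individuals were randomised by a computer-generated list", and gives no ratio or blocking. Under Concomitant therapy it adds: "Anti-hypertensive therapy will be titrated throughout the study period to maintain the blood pressure below 130 / 80 mmHg".

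Protocol, Statistical analysis: the quantity tested is "The change in proteinuria, renal function and other inflammatory markers before and after treatment". The method is fixed in the same sentence, which says that these values "will be compared by paired Student’s t test or Wilcoxon’s matched-pairs signed-rank test as appropriate". Neither period nor sequence appears in the analysis anywhere in the protocol. The sample-size paragraph (Justification) also rests on a two-sided paired t-test.

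A separate statistical analysis plan may exist. The protocol itself names the test, however, so this is a stated choice and not a detail left for later.

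**The concern.** A pooled paired test treats every within-patient difference as centred on the drug effect. In a two-sequence cross-over that is true only if nothing else changes between periods. Titration of background therapy over the whole study is one plausible reason for a change, and the 4-week washout of study drug does not restore the background regimen.

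If there is such a shift, the two sequences have different centres. Pooling them has two consequences:

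- The spread between the centres is counted as random error, so the test becomes conservative and loses power.
- When the sequences contribute unequal numbers of completers, part of the shift is counted as drug effect.

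The randomised sequence is known for every patient and can be used to remove both.

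**Working it through.** **Inputs from the protocol.** "We expect baseline proteinuria to be around 2.0 ± 0.75 g:g-Cr" gives a mean of 2.0 and an SD of 0.75. The planned effect is 20% of 2.0 = 0.40 g/g. N = 57, power 80%, two-sided alpha 0.05, paired t-test.

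**Assumed, because the protocol gives no figure.** Period shift p = 0, 0.2 or 0.4 g/g; sequence split 29/28 (the nearest to equal for 57) or 24/28 completers.

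**Reproducing the sample size.** With SDd = 0.75 × √2 = 1.061 (zero within-patient correlation):

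- n = (1.061 × (1.960 + 0.842)/0.40)² ≈ 55.2, so 56 by the normal formula. The t-based answer is 58, and power at 57 is 79.9%.
- With SDd = 0.75 the formula gives 28 (normal) or 30 (t), which does not match.

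The stated 57 therefore corresponds to SDd = 1.061, which is used below.

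**Model.** Let d = proteinuria on placebo minus proteinuria on aliskiren, τ the drug effect, and p the fall from period 1 to period 2. Then d centres on τ − p in sequence aliskiren–placebo (AP) and on τ + p in sequence placebo–aliskiren (PA).

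- Plain paired estimate: expectation τ + p × (nPA − nAP)/N.
- Variance of the pooled d: SDd² + p² × 4·nAP·nPA/(N(N − 1)), about SDd² + p².
- Period-adjusted estimate: the average of the two sequence means. It is unbiased for τ, with SE = (SDd/2) × √(1/nAP + 1/nPA).

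**Standard error at 29/28.** The factor 4 × 29 × 28/(57 × 56) is 1.0175.

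- p = 0: √(1.125/57) = 0.1405.
- p = 0.2: √((1.125 + 0.0407)/57) = 0.1430, up 1.8%.
- p = 0.4: √((1.125 + 0.1628)/57) = 0.1503, up 7.0%.
- Period-adjusted, any p: 0.5303 × √(1/29 + 1/28) = 0.1405.

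**Simulated power at τ = 0.40 and type I error at τ = 0** (40,000 runs; ranges cover which sequence has 29):

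| p (g/g) | Power, plain paired t | Power, period-adjusted | Type I error, plain |
|---|---|---|---|
| 0 | about 80% | about 80% | about 5% |
| 0.2 | about 78–80% | about 80% | about 4.5% |
| 0.4 | about 74–77% | about 80% | about 3.5% |

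**Bias of the plain estimate.**

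- 29/28: 0.2 × 1/57 = 0.004 and 0.4 × 1/57 = 0.007 g/g.
- 24/28: 0.2 × 4/52 = 0.015 and 0.4 × 4/52 = 0.031 g/g, which is 4% to 8% of the planned 0.40. The sign depends on the direction of p and on which sequence loses more patients, so power can move either way.
- Period-adjusted: zero.

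The figures are for the t test. The signed-rank test pools the same differences and omits the same term; it was not simulated.

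**The case against.** The case against rating this highly is strong, and most of it stands.

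**Both harms are conditional.** A reader might infer that the standard error is simply too wide and the estimate simply biased. The documents do not support that. Each needs a non-zero period effect, bias also needs unequal sequences, and the protocol quantifies neither. It describes patients as stable on an ACE inhibitor or ARB before entry, and a p of 0.4 g/g would be a drift as large as the whole planned drug effect.

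**The direction is not documented.** One might infer that period 2 begins on heavier background treatment. The protocol says only that therapy is titrated to hold a blood-pressure target, which could move either way. The Background says aliskiren lowers blood pressure, so titration may differ between aliskiren and placebo periods. That part is not a shift common to both sequences, and a period term does not remove it.

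**Larger figures can be produced, but not from the plan's own numbers.**

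- At p = 0.4 and within-patient correlation 0.7 (SDd 0.581), power falls to 53% against 72% adjusted. This uses a 0.2 g/g effect, half the planned one. At 0.40 g/g both analyses exceed 99%.
- A type I error of 12.7% arises at p = 0.4 with a 38/19 split. Under simple 1:1 allocation of 57, a split at least that uneven has probability about 1.6% before withdrawals. At 24/28 type I error stays at or below 5%.

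**A different reading of the test would be worse.** Taken literally, the Statistical analysis section compares values before and after treatment. A time trend would then bias the result even with equal sequences. That is a question of which contrast is tested. This point takes the kinder reading, aliskiren versus placebo within patient.

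What survives is that a design factor is left out of a named test, and that using it costs almost nothing.

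**Conclusion.** The point holds as an advisable improvement, not as something that must be fixed. The plain paired test is inefficient when the periods differ, and near balance its error is conservative. On the plan's own effect and the SDd that reproduces 57, the power loss at 29/28 is at most about 2 points for p = 0.2 g/g and about 3 to 6 points for p = 0.4 g/g. Power starts at 79.9%, so there is no reserve to absorb it. Bias is negligible at 29/28 and small at 24/28; it becomes material only with marked imbalance. The protocol states no blocking, and it withdraws patients for intolerable adverse events, doubling of creatinine and non-compliance, so imbalance is possible but not shown.

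These sizes rest on assumed period shifts and splits, and on zero within-patient correlation as implied by the sample size. With p = 0 neither harm exists.

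**What to change.** In the Statistical analysis section, state that the primary comparison is aliskiren versus placebo, analysed by randomised sequence. Either of these will do:

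- a mixed model with treatment, period and sequence as fixed effects and patient as random effect; or
- the two-sample comparison of within-patient period differences between the two sequences (Hills–Armitage).

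If the data are clearly non-normal, apply the Wilcoxon rank-sum test to the period differences by sequence in place of the signed-rank test.

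The text should also say that the period term removes only a shift common to both sequences. It does not remove changes in background therapy that depend on the treatment received. No change to the titration rule is implied.

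The cost is a few lines of wording and one degree of freedom, with no extra patients or visits. With p = 0 and a 29/28 split there is no measurable loss of power (about 80% either way). At 33/24 the adjustment costs about one point (78.7% against 79.7%).

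### Blood pressure titration during the study does not hold the ACE inhibitor or ARB fixed, so drugs that lower proteinuria may change between periods; the expected bias is toward no effect, but its direction is not certain and its size is unknown

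*Protocol*

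**What the plan says.** The paragraph on concomitant therapy (Protocol, Treatment regimen and dosage adjustment) has two sentences. On background treatment: "Prior to enrollment, all of the patients will be stable while receiving ACE inhibitor or ARB". On conduct: "Anti-hypertensive therapy will be titrated throughout the study period to maintain the blood pressure below 130 / 80 mmHg". Neither says that the ACE inhibitor or ARB dose stays fixed after enrolment, names the classes to be used for titration, or bars a second RAS blocker.

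Under Inclusion criteria every patient "requires anti-hypertensive therapy" and has had at least 3 months of an ACE inhibitor or ARB, at no stated dose. Under Exclusion criteria two entries touch other drugs that act on proteinuria: "Previous treatment with fish oil, steroid, cytotoxic agents, or aldosterone antagonist" and "History of treatment with other drugs that may affect proteinuria within past 2 years". Both concern history at entry.

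The Background supplies the two facts that make this matter. On the study drug: "Renin inhibition with aliskiren lowers blood pressure in hypertensive patients". On ACE inhibitors and ARBs, they "reduce proteinuria in short-term trials". The primary end point is the change in proteinuria and albuminuria, and under End points: "Average levels proteinuria and albuminuria levels at –4 and 0 week will be taken as the baseline".

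**The concern.** Titration follows measured blood pressure, and aliskiren is expected to lower blood pressure. Step-ups should therefore be more frequent on placebo, or in the washout after aliskiren. If a step-up uses a RAS-active drug, it lowers proteinuria in the period that serves as the control. Blinding does not prevent this, because the trigger is the blood pressure reading and not knowledge of the allocation. The 4-week washout removes the study drug, not an added or increased co-medication.

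The sample size assumes a 20% reduction from aliskiren additional to losartan 100 mg. That presumes a comparable RAS-blocking background in both periods, which the concomitant therapy paragraph does not secure. At stake is a diluted treatment contrast on the primary end point. An analysis plan cannot undo treatment already given, so the rule belongs in the Protocol.

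**Working it through.** **Inputs from the Protocol (Justification).** Baseline proteinuria 2.0 ± 0.75 g/g-Cr, 20% reduction, N = 57, 80% power, two-sided alpha 0.05, paired t-test. No SD of within-patient differences is stated.

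**The plan's own figure.** Difference = 0.20 × 2.0 = 0.40 g/g-Cr. SD of differences = 0.75 × √(2(1 − r)), where r is the within-patient correlation. At r = 0 this is 1.06, and the noncentral t gives N = 58, with 79.9% power at 57. So 57 reproduces within rounding if r = 0. Using 0.75 directly as the SD of differences gives N = 30, which does not.

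**Assumptions for the illustration (none is in the Protocol).** A share p of patients has RAS-active therapy raised on placebo or in the washout after aliskiren. Each step-up lowers proteinuria by a fraction q and persists. Change is measured from the week -4 and 0 baseline. In a placebo-first patient the step-up then carries into the aliskiren period and cancels, so only the aliskiren-first half is affected.

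**Formula.** Apparent reduction = 1 − exp[ln 0.8 − 0.5 × p × ln(1 − q)].

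Example, p = 30%, q = 20%: ln 0.8 = −0.2231; 0.5 × 0.3 × (−0.2231) = −0.0335; −0.2231 + 0.0335 = −0.1897 (from unrounded terms); 1 − exp(−0.1897) = 17.3%. Mean difference = 2.0 × 0.173 = 0.346 g/g-Cr.

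| p, q | Apparent reduction | Difference (g/g-Cr) | Power, r = 0 (SD 1.06) | Power, r = 0.3 (SD 0.89) | Power, r = 0.5 (SD 0.75) |
|---|---|---|---|---|---|
| no step-ups | 20.0% | 0.400 | 79.9% | 91.7% | 97.7% |
| 10%, 10% | 19.6% | 0.392 | 78.2% | 90.6% | 97.2% |
| 20%, 15% | 18.7% | 0.374 | 74.4% | 87.8% | 95.9% |
| 30%, 20% | 17.3% | 0.346 | 67.6% | 82.4% | 92.8% |
| 50%, 20% | 15.4% | 0.308 | 57.8% | 73.1% | 86.2% |

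**How many step-ups would bring power below 80%?** Under the same model, at r = 0.3, p must reach about 36% (q = 20%), 49% (q = 15%) or 76% (q = 10%). At r = 0.5, it must reach about 63% (q = 20%) or 87% (q = 15%); at q = 10% it never does.

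**Sensitivity to the carry-over assumption.** Suppose there is no cancellation, and an excess share f of all patients is stepped up in the placebo period only, each by a fraction g. The bias is then f × g × 2.0 g/g-Cr. With f = 5%, g = 10% it is 0.01 (power 77.9% at SD 1.06; 97.1% at SD 0.75). With f = 10%, g = 20% it is 0.04 (71.2%; 94.5%). With f = 30%, g = 30% it is 0.18 (33.7%; 58.6%). The answer depends on shares and effects that the Protocol does not give.

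**Direction.** Three cases follow from the text:
- Aliskiren-first, step-up after withdrawal: placebo-period proteinuria falls and the contrast shrinks.
- Placebo-first, persisting step-up: both periods are affected and it largely cancels.
- The Statistical analysis section compares values from ahead of treatment with values following it, by paired tests. If that is read as a comparison within aliskiren alone, a step-up during aliskiren adds to the apparent fall and inflates the effect.

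**The case against.** The case against rests on four points.

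- **The Protocol does not direct RAS-active titration.** It lists ACE inhibitor or ARB treatment apart from anti-hypertensive therapy, both in the inclusion criteria and in the concomitant therapy paragraph. A reasonable reading is a stable RAS background with other agents titrated. The exclusions point to the same intent. This stands in part: a reader might infer that the plan calls for raising the ACE inhibitor or ARB, and it does not. But it permits it, and entry criteria do not bind on study. An added aldosterone antagonist is the least likely case.
- **The relevant share of patients is narrow.** With persisting step-ups, what counts is mainly new RAS-active step-ups after aliskiren is withdrawn, in patients returning toward a state in which they were already stable. Shares of 30% to 50% look extreme, and q = 20% makes a step-up as strong as the whole assumed aliskiren effect. This stands and limits the size.
- **The low powers come from r = 0.** That is doubtful in a crossover of patients selected for proteinuria above 1 g in three consecutive samples. This also stands, although r = 0 is the paired-test assumption that reproduces 57.
- **A common target below 130/80 mmHg is legitimate** for seeking an effect beyond blood pressure. This is accepted; only the choice of drugs used to reach it is in question.

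**Conclusion.** The concern holds as a gap in a conduct rule. RAS-active drugs that lower the primary outcome may be raised or added on study in response to a blood pressure that aliskiren itself affects. For the aliskiren-placebo contrast the expected net bias is toward the null.

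A reader might infer that the error can only be conservative, so that a positive result is safe. The documents do not support that: placebo-first step-ups largely cancel, and a within-aliskiren before-after comparison, which is one reading of the Statistical analysis section, would be inflated. A reader might also infer from the worst rows that the trial is seriously underpowered for this reason. That is not supported either. The Protocol gives no blood pressure distribution, entry dose or titration rate, so p, q and r are assumptions. In the mildest row the apparent reduction is 19.6% against 20%. With r = 0.5 power stays above 80% in every row of the table. The size cannot be derived and may be small.

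The change is still worth making, because it is cheap and the confounding cannot be cleanly removed afterwards. Confidence is medium.

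**What to change.** Keep the common target of below 130/80 mmHg and amend the concomitant therapy paragraph to state that:

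1. the ACE inhibitor or ARB drug and dose stay as at entry from week -4 to week 36, except for reductions or stops for safety;
2. no second RAS blocker and no aldosterone antagonist is added in that time;
3. titration up uses other anti-hypertensive classes, and if blood pressure is low those are reduced first, before the ACE inhibitor or ARB.

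Record any RAS-active change by treatment period, including safety reductions. These may be more frequent on aliskiren and would also shrink the contrast.

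The cost is two or three sentences, with no extra patients, visits or tests. The downside is that investigators have fewer agents for reaching the target, and safety reductions on aliskiren remain possible.

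### The only defined baseline (weeks −4 and 0) predates period 2 by 20 weeks or more, so before-after changes pooled over periods absorb drift; the aliskiren-minus-placebo contrast does not

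*Protocol*

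**What the plan says.** The End points paragraph of the Protocol states: "Primary end point of the study is the change in the degree of proteinuria and albuminuria". It then sets the reference value: "Average levels proteinuria and albuminuria levels at –4 and 0 week will be taken as the baseline". No other baseline is defined, and this one is not limited to period 1.

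The Treatment regimen section gives the design as active drug or "placebo for 16 weeks, followed by a washout period of 4 weeks, then crossed over to either placebo or aliskiren for another 16 weeks". Period 2 therefore runs from week 20 to week 36. Week 20 is a scheduled visit, and each visit includes "early morning urine collection for protein-to-creatinine and albumin-to-creatinine ratio", so an end-of-washout value is collected.

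Two further statements bear on whether weeks −4 and 0 still describe the patient at week 20. On the washout, the Protocol relies on a published study in type 2 diabetes to say that "a washout period of 4-weeks would be sufficient and baseline proteinuria level could be re-established". On background treatment: "Anti-hypertensive therapy will be titrated throughout the study period to maintain the blood pressure below 130 / 80 mmHg".

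The Statistical analysis section says that the change in proteinuria and the other markers "before and after treatment will be compared by paired Student’s t test or Wilcoxon’s matched-pairs signed-rank test as appropriate". It names no aliskiren-versus-placebo contrast and no period term.

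**The concern.** In a cross-over trial, a before-after change has a clear meaning only if the before value belongs to the period being measured. Here it does so for period 1 only.

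For patients who take aliskiren second, the before value precedes the whole placebo period, the washout and 20 weeks of blood-pressure titration. Anything that moved proteinuria in that time is counted as aliskiren change. For patients who take placebo second, the before value precedes aliskiren exposure, so any lasting effect of period 1 would be counted as placebo change.

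The week 20 value has no stated role as a baseline. Yet the schedule treats it as the counterpart of week 0: visits at weeks 20, 22, 24, 28, 32 and 36 repeat the spacing of weeks 0, 2, 4, 8, 12 and 16, and the gene-expression and serum-marker samples at weeks 20, 24 and 36 mirror those at weeks 0, 4 and 16. At stake is the size of the reported aliskiren change, which is the primary endpoint as worded.

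**Working it through.** **Age of the baseline.** Period 2 starts at week 16 + 4 = 20.

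| Time point | Age of week 0 sample | Age of week −4 sample |
| --- | --- | --- |
| End of period 1 (week 16) | 16 weeks | 20 weeks |
| Start of period 2 (week 20) | 20 weeks | 24 weeks |
| End of period 2 (week 36) | 36 weeks | 40 weeks |

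With week 20 as the period 2 baseline, the gap to week 36 is 16 weeks, the same as from week 0 to week 16.

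**Scale of the effect.** The Justification section expects baseline proteinuria of 2.0 ± 0.75 g/g-Cr and a 20% reduction, so τ = −0.20 × 2.0 = −0.40 g/g-Cr. The stated sample size of 57 is approximately reproduced with SD of the difference 0.75 × √2 = 1.061: a paired t-test then needs 58, and 57 gives 79.9% power. Baseline timing is not an input to that calculation, so this point does not alter it.

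**Drift.** Let D be a shift in proteinuria between weeks −4/0 and period 2 that is unrelated to aliskiren. The Protocol gives no value; D = −0.2, 0 and +0.2 g/g-Cr are assumed. Half the patients take aliskiren second. With the fixed baseline:

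- aliskiren change in period 1 = τ
- aliskiren change in period 2 = τ + D
- pooled aliskiren change = τ + D/2
- pooled placebo change = D/2
- aliskiren minus placebo = (τ + D/2) − D/2 = τ

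| D | Period 2 aliskiren change | Pooled aliskiren change | Pooled placebo change | Aliskiren minus placebo |
| --- | --- | --- | --- | --- |
| −0.2 | −0.60 | −0.50 | −0.10 | −0.40 |
| 0 | −0.40 | −0.40 | 0 | −0.40 |
| +0.2 | −0.20 | −0.30 | +0.10 | −0.40 |

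With a week 20 baseline, the period 2 aliskiren change is −0.40 in all three rows. A simulation with these inputs gave the same figures to within 0.002.

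The last column holds because, for each patient, (Y_A − B) − (Y_P − B) = Y_A − Y_P: a shared baseline B drops out. If a share p takes aliskiren second, the unadjusted contrast is τ + (2p − 1)D. Since 57 is odd, the closest split is 29/28, which leaves (1/57) × 0.2 = 0.0035 g/g-Cr. A period term removes it.

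**Cost of subtracting week 20 in the contrast.** Assume a between-patient SD of 0.60 and an independent residual SD of 0.45 (0.36 + 0.2025 = 0.5625 = 0.75², matching the Protocol's SD).

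- Fixed baseline: variance 2 × 0.2025 = 0.405, SD 0.636. Drift of ±0.2 without period adjustment adds 0.04, giving SD 0.667.
- Period baselines subtracted: variance 0.2025 × (1 + 1 + 0.5 + 1) = 0.709, SD 0.842, which is 26% to 32% larger.
- Assumed 25% carry-over at week 20, gone by week 36: the baseline is 0.25 × 0.40 = 0.10 too low in patients who took aliskiren first. The pooled placebo change becomes +0.05 and the contrast −0.45. With the fixed baseline it stays at −0.40.

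Entered as a covariate, the within-patient baseline difference is uncorrelated with the outcome difference under this model. Its expected coefficient is zero, the contrast stays near −0.40, and precision is neither lost nor gained.

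**The case against.** The strongest reply is that the harm is nil in the comparison a placebo-controlled cross-over exists to make. The shared baseline cancels there, so the fault would lie in the before-after test and not in the baseline rule. That stands. A reader might infer that the trial's treatment comparison is biased by a quarter of its target effect (0.1/0.4). The documents do not support that: the 0.1 g/g-Cr belongs to the pooled within-aliskiren change, whereas the 20% in the Justification section is an additional reduction on top of losartan. For the contrast the bias is zero, and for the before-after change it may inflate or shrink the effect.

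A reader might also infer that carry-over is present. The Protocol asserts a sufficient washout, and nothing in it shows otherwise. By week 36, patients who take placebo second are 20 weeks past their last aliskiren dose. If a residual effect exists, it should be largest at week 20, so that value is no safe substitute in the contrast.

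The text does not say in words that weeks −4/0 serve period 2, and before treatment could be read as before each period. But the rule is unrestricted and is the only one given, so this is a reason to state the rule for each period. Lastly, a week 20 baseline leaves drift within each 16-week period in a before-after change. That also stands, and it is why the contrast with placebo should come first.

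**Conclusion.** The point holds for the before-after analysis that the Protocol describes. There, the fixed baseline lets 20 or more weeks of unrelated change into the period 2 result. With drift of ±0.2 g/g-Cr (10% of the expected baseline), the pooled aliskiren change is off by 0.1 in either direction. The drift values are assumptions; the documents give no estimate. The formula D/2 scales to any other value, given equal sequences.

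It does not hold for a within-patient aliskiren-minus-placebo contrast with balanced sequences, where the baseline has no influence. The rule is thus either harmful or without effect, depending on which analysis is run, and the Protocol describes the one where it harms. The correction is worth making and is modest. The SAP is not at hand and may settle some of this, but the baseline rule and the test are both stated in the Protocol.

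**What to change.** 1. Make the primary analysis the within-patient aliskiren-versus-placebo difference in on-treatment values, adjusted for period.
2. For any reported before-after change, use the mean of weeks −4 and 0 as the baseline for period 1 and week 20 for period 2.
3. If period baselines enter the primary model, enter their within-patient difference as a covariate. Do not subtract them.
4. Tabulate week 20 against weeks −4/0 by sequence, as a descriptive check of the washout assumption in this non-diabetic population. Do not use it as a carry-over pretest that decides the analysis.

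No visit, sample or change in the stated sample size is needed. The Statistical analysis text must change along with the endpoint wording. Week 20 is a single sample, whereas the period 1 baseline averages two. It is also the value most exposed to any residual aliskiren effect. The covariate brought no gain in precision under the model above; it could help if residuals are correlated within a period, but it would then also carry over part of any contamination of week 20.
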